## Abstract

**Background:**

Lisfranc injuries are known to be rare and often overlooked injuries that can cause long-term disability and pain when missed or treated incorrectly. The wide variety of Lisfranc injuries ranges from subtle ligament distensions to open fracture dislocations. The treatment of Lisfranc joint injuries is still controversial and very little is known about what types of injury can be treated nonoperatively. The current literature provides only two randomized studies on dislocated Lisfranc injuries. These studies have shown that primary arthrodesis (PA) leads to a similar or better outcome and results in fewer secondary operations when compared with open reduction and internal fixation (ORIF) in ligamentous injuries. There have been no previous randomized studies of the nonoperative versus operative treatment of Lisfranc injuries. Therefore, the purpose of this study is to compare the operative and nonoperative treatment of non-dislocated Lisfranc injuries and to compare the ORIF and PA treatment of dislocated Lisfranc injuries.

**Methods:**

This study is a prospective, randomized, national multi-center trial. The trial comprises two strata: Stratum I compares cast-immobilization versus open reduction and internal fixation (ORIF) treatment of non-dislocated Lisfranc joint injuries. Stratum II compares PA versus ORIF in the treatment of dislocated injuries of the Lisfranc joint. The main hypothesis of stratum I is that the nonoperative treatment of non-dislocated Lisfranc injuries achieves a similar outcome compared with operative treatment (ORIF). The hypothesis of stratum II is that PA of dislocated Lisfranc injuries yields a similar functional outcome compared with ORIF, but that PA results in fewer secondary operations than ORIF. The main outcome measure is the American Orthopaedic Foot and Ankle Society (AOFAS) Midfoot score and the secondary outcome measures are Visual-Analogue-Scale Foot and Ankle (VAS-FA), Visual-Analogue-Scale (VAS), rate of secondary operations and other treatment-related complications. The results will be analyzed after the 2-year follow-up period.

**Discussion:**

This publication presents a prospective, randomized, national multi-center trial study protocol. It provides details of patient flow, randomization, aftercare and methods of analysis of the material and ways to present and publish the results.

**Trial registration:**

ClinicalTrials.gov identifier: NCT02953067 24.10.2016.

## Background

Named after Jaques Lisfranc, an eighteenth century surgeon who performed the first foot amputations at the tarsometatarsal (TMT) joint, the Lisfranc joint is an anatomic area where a broad spectrum of injuries from subtle distensions to open fracture dislocations occur [1, 2]. The incidence of Lisfranc injuries is estimated to be 1/55000/year and they are believed to account for 0.2% of all fractures [3, 4]. These figures have, however, been challenged as up to 24% of Lisfranc injuries are either misdiagnosed or overlooked during initial evaluation [5–7]. Injuries to the Lisfranc joint occur most often during the third decade of life and men are 2 to 4 times more likely to suffer from these injuries than women [8]. Lisfranc injuries are caused either by direct or indirect forces to the foot [9]. Indirect injuries are more common and occur during bending or twisting movements applied to the midfoot [9]. Injuries caused by direct forces are often induced by a heavy object falling on top of the foot or by crush injuries, such as in motor vehicle accidents [6, 7]. A wide spectrum of injuries to the TMT and interrelated joints have been recognized, and range from severely dislocated high-energy open injuries to minor midfoot sprains suffered during sports activities [10–12].

An untreated or inadequately treated Lisfranc injury results in multiple late complications, the severity of which depends on the severity of the primary injury [13]. The most common complications are painful instability of the joint, malformation and arthritis [5]. All these complications can lead to remarkable dysfunction and foot pain [5]. Secondary arthrodesis may be used to treat these injuries, but the outcome is poorer the longer the treatment is delayed [14–16]. Therefore, the initial recognition of these injuries is a crucial step in ensuring optimal treatment is provided.

### Diagnosis and treatment

Fractures of the Lisfranc joint are known to be rare and are often overlooked [7, 17–19]. Approximately 20 to 24% of these fractures are missed at initial evaluation [5, 7]. High-energy injuries are often the most obvious due to traumatic history and very apparent clinical findings [20]. Low-energy injuries, however, are harder to detect because of less traumatic history and less apparent clinical findings [21]. Typical clinical findings of fracture of the Lisfranc joint are a swollen midfoot, tenderness and pain in the midfoot during passive movements and weight-bearing [22], plantar ecchymosis [23] and an extended space between the first and second toe seen in x-ray radiographs that is also known as the ‘gap’ sign [24].

Although sensitivity is relatively low when compared with CT-imaging, primary diagnosis of Lisfranc injuries is usually based on plain x-ray imaging [7]. False-negative findings on x-ray radiographs may be the result of weight-bearing not tolerated due to pain [6]. A typical finding ‘fleck sign’ in plain x-ray radiographs, an avulsion of intra-articular bone, is estimated to be detectable in 90% of cases where the dislocation between the first and second metatarsal is greater than 4 mm [5]. As the radiographic findings of Lisfranc injuries can be subtle, CT is an important imaging modality in detecting these injuries, and furthermore serves as a useful tool for preoperative planning [25, 26]. Although the current literature introduces classifications that provide general characteristics for Lisfranc injuries, none of the classifications are useful in predicting treatment or outcome of a Lisfranc injury [27]. Moreover, the current literature fails to offer a classification based on computed tomography.

Due to the diversity of injuries, there is no single evidence-based policy for treating all Lisfranc injuries in a similar manner [28]. Nowadays, there is strong consensus that in dislocated injuries it is crucial to achieve exact anatomic reduction and stable internal fixation, which is best obtained with open reduction and screw fixation (ORIF) [5, 29]. However, even after appropriate treatment with ORIF, up to 40 to 94% of patients will develop post-traumatic arthritis [5, 13, 30, 31], necessitating conversion to an arthrodesis to relieve pain [14–16]. To prevent the need for secondary operations and the development of post-traumatic arthritis, primary arthrodesis (PA) is suggested [30, 32–34]. The treatment of non-dislocated injuries, in turn, is controversial [29, 35–38]. Some stable injuries might need activity modification only, but surgery is often recommended for even minimally displaced injuries [5, 29]. There is general agreement, however, that poor functional results are commonly correlated with a delay in diagnosis or the inadequate treatment of unstable or dislocated injuries [19, 27].

Fixation with screws is the primary fixation technique used to treat dislocated Lisfranc injuries [13, 31]. K-wire fixation [5, 12, 39, 40] and screw fixation [13, 22, 41, 42] are both controversial, but the higher failure rates associated with K-wire fixation have led to an increase in screw fixation [13, 43, 44]. Another fixation technique, dorsal plate fixation, has been reported to produce similar results as ORIF [45]. An advantage of dorsal plate fixation is that the plate causes no damage to the articular surface. However, soft-tissue irritation may be more prevalent, and second surgery is often needed to remove the plates [45].

There is, however, no general agreement on what is the correct nonoperative protocol for treating non-dislocated Lisfranc injuries. In their review, Myerson and Cerrato [11] concluded that if the foot remains stable in weight-bearing radiographs 2 weeks after the injury, the injury can be treated with immobilization in a boot and weight-bearing is permitted as tolerated until the boot is removed at six to eight weeks. In the study by Nunley & Vertullo [29], stable injuries were treated nonoperatively. Furthermore, it was suggested that treatment begin with a non-weight-bearing cast for 6 weeks. If the patient is painless at 6 weeks, treatment should continue with a gradual return to normal function with a weight-bearing orthosis for the following 4 weeks.

The commonly used postoperative protocol is nearly identical to nonoperative treatment. In their study, Ly & Coetzee [30] used a short leg splint for 2 weeks followed by a short leg cast for four to six weeks. The patients advanced to full weight-bearing during the following 4 weeks while wearing a prefabricated fracture boot. In the study by Henning et al. [33], weight-bearing began at three months with a controlled ankle motion walker.

Interestingly, there are several opinions about postoperative implant removal. Some studies suggest routine screw removal at 8 or 12 weeks [31, 33, 46, 47], while others prefer routine removal only after the recovery is complete or only if the screws cause irritation or pain [48–50]. Ahmad and Jones [51] have suggested the use of bioabsorbable screws to remove the need for screw removal. In addition, bioabsorbable screws achieve similar functional results compared with metal screws.

### Evaluation of treatment

Most of the previous studies have used Patient Reported Outcome Measures (PROMs) to evaluate treatment. The most common PROM used in Lisfranc injury studies is the American Orthopaedic Foot and Ankle Society Midfoot Score (AOFAS) [13, 28, 30, 38, 47]. Other commonly used PROMs include Visual-Analogue-Scale Foot and Ankle (VAS-FA) [52] (also validated in the Finnish language [53]), Visual-Analogue-Scale (VAS) [28], Short Form 36 (SF-36) [28, 33], Baltimore Painful Foot Score (PFS) [31], Short Musculoskeletal Function Assessment (SMFA) [33], long-form Musculoskeletal Function Assessment (MFA) [13], the Maryland foot score [47] and activities of daily living (ADL) [47]. In our study, we decided to use AOFAS because it is the most commonly used PROM for Lisfranc injuries and VAS-FA as it is validated in the Finnish language [53].

### Previous studies

The literature does not provide any prospective randomized controlled studies on the nonoperative versus the operative treatment of Lisfranc injuries. Current knowledge is based on a few case-series [35, 37] and retrospective studies [5, 22, 38]. Nunley and Vertullo [29] suggested in their series of midfoot sprains in athletes that only totally non-dislocated sprain injuries should be treated nonoperatively, and that all injuries where the diastasis between the first and second metatarsal is 2 mm or more would benefit from ORIF. Myerson et al. [5] were the first to study the nonoperative treatment of Lisfranc injury. In their study, only 5 out of a total of 52 patients were treated nonoperatively, and these patients received the treatment unintentionally, due to incorrect diagnosis. Of these five patients, four resulted in a poor result and one resulted in a fair result. Curtis et al. [22] organized a retrospective study of the treatment of 19 athletes with Lisfranc injuries. Only 14 stable injuries were treated nonoperatively. An excellent functional result was obtained with six patients, a good result with three patients, a fair result in four and a poor result with one patient. An excellent result implied the absence of symptoms and signs; a good result implied minor symptoms or signs; a fair result implied residual signs of symptoms with some disability, and a poor result implied marked symptoms or signs with limitation of function and a request for further treatment, such as arthrodesis. The treatment protocol between patients differed from “none” to “cast for ten weeks”. Crates et al. [38] studied nonoperative treatment and operative treatment after the failed nonoperative treatment of subtle Lisfranc injuries in 36 patients. The nonoperative protocol consisted of 6 weeks of a short leg walking orthosis and weight-bearing was progressed as tolerated. Progressed weight-bearing in an orthotic was begun after boot removal. Nonoperative treatment was successful in 16 patients, and the treatment failed in 20 patients. The mean AOFAS midfoot score in the successfully treated patients was 62 (49–72) before treatment and 75 (53–100) after treatment.

There have only been two previous prospective randomized studies on ORIF vs PA. Ly and Coetzee [30] randomly assigned 41 patients with ligamentous Lisfranc injuries to either an ORIF group or a PA group. The PA group had a slightly better functional outcome (AOFAS score 88 vs. 69), a higher return to preinjury activity level (92% vs. 65%), a lower rate of revision surgery and less pain in the final follow-up. Implant removal due to prominent or painful screws was performed on 16 of the 20 patients in the ORIF group and on 4 of the 21 patients in the PA group. The implant removal was only performed due to painful hardware, on average at 6.5 months (range: from five to ten months). Follow-up radiographs showed loss of correction, increasing deformity, and degenerative joint disease in 15 of the 20 patients in the ORIF group and 7 of them required conversion to an arthrodesis. In the PA group, one patient had delayed union at seventeen weeks and one patient required a revision arthrodesis with bone graft. One patient suffered from a post-traumatic intrinsic compartment syndrome that resulted in claw toes. In the study by Henning et al. [33], 40 patients with acute Lisfranc joint fractures or fracture dislocations were randomized to primary ORIF or PA. A total of 8 patients dropped out before 3-months follow-up. There was a significantly higher rate of secondary surgery in the ORIF group. Statistically significant differences were not found in physical functioning with regard to SF-36 or SMFA scores at any follow-up time interval. In their systematic review and meta-analysis, Smith et al. [34] concluded that ORIF has a higher risk of implant removal compared with PA (risk ratio 0.23 (0.11–0.45) *p* < 0.001), although there were no statistically significant differences in revision surgery, PROMs or non-anatomic alignment. Cochran et al. [32] organized a retrospective comparative cohort study on PA versus ORIF in young athletic military personnel with low-energy Lisfranc injury. In their study, PA resulted in a faster return to military service, a lower implant removal rate and better fitness scores after 1 year.

In conclusion, PA seems to result in less secondary surgery, less implant removal and a faster return to activity. There is some evidence of a better functional outcome after arthrodesis, but the result is still controversial. Nevertheless, the current overall evidence slightly favors arthrodesis as a primary treatment of dislocated Lisfranc injuries.

### Aims of this study

The aim of this two-armed randomized controlled trial is to I) compare nonoperative treatment with ORIF in non-dislocated Lisfranc injuries and II) to compare ORIF with PA in dislocated Lisfranc injuries.

## Methods/design

The study is a prospective, randomized, national multicenter trial. The trial centers are Tampere University Hospital and Seinäjoki Central Hospital. The trial has been designed to compare the nonoperative and operative treatment of Lisfranc injuries. The trial includes two strata: Stratum I compares nonoperative treatment and operative treatment with ORIF for non-dislocated Lisfranc injuries. Stratum II compares ORIF and PA in dislocated Lisfranc injuries.

The primary outcome in this study is the AOFAS [54] measured after 6, 12 and 24 months. The secondary measured outcomes after 6, 12 and 24 months are VAS [55], VAS-FA [52], number of secondary operations (implant removal, secondary arthrodesis) and number of other treatment-related complications.

### Hypotheses

Our primary hypotheses in the study are the following:i)The hypothesis of stratum I is that nonoperative treatment of non-dislocated Lisfranc injuries yields better outcome in terms of AOFAS, VAS and VAS-FA score compared with operative treatment (ORIF).ii)The hypothesis of stratum II is that PA of dislocated Lisfranc injuries yields better functional outcome in terms of AOFAS, VAS and VAS-FA score compared with ORIF, and PA results in fewer secondary operations than ORIF.

The results of both strata will be analyzed and reported separately.

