### Statistical analysis

The baseline characteristics will be reported as mean (standard deviation), median (quartiles) or proportion. Study groups will be compared using t-test, Mann-Whitney U or Fisher’s exact test. Primary (AOFAS) and secondary outcomes (VAS-FA, VAS, complications, secondary surgery) will be compared at 12 months and 24 months using the Mann-Whitney U test. The results will be presented with 95% confidence intervals, and therefore a *p*-value of < 0.05 will be considered statistically significant. The data will be analyzed according to the intention-to-treat principle, assuming the patients change group during the study. The statistical analysis will be performed with SPSS© version 22.

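### Each stratum has two conflicting main hypotheses, *similar* in the Abstract and *better* in the Hypotheses section, and the planned test of difference, with no margin, cannot establish *similar*

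*Protocol article*

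**What the plan says.** Abstract, Methods: the main hypothesis of stratum I is that "the nonoperative treatment of non-dislocated Lisfranc injuries achieves a similar outcome compared with operative treatment (ORIF". For stratum II it is that "PA of dislocated Lisfranc injuries yields a similar functional outcome compared with ORIF, but that PA results in fewer secondary operations than ORIF".

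Hypotheses section, for the same two comparisons: in stratum I "nonoperative treatment of non-dislocated Lisfranc injuries yields better outcome in terms of AOFAS, VAS and VAS-FA score compared with operative treatment (ORIF", and in stratum II "PA of dislocated Lisfranc injuries yields better functional outcome in terms of AOFAS, VAS and VAS-FA score compared with ORIF". The expectation of fewer secondary operations after PA is the same in both places.

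The section on the aims of the study speaks only of comparing the treatments, so it does not settle which version governs.

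Statistical analysis: the primary and secondary outcomes "will be compared at 12 months and 24 months using the Mann-Whitney U test", with p < 0.05 as the criterion. It adds: "The results will be presented with 95% confidence intervals". The article gives no non-inferiority or equivalence margin and no rule for concluding that outcomes are similar.

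Power analysis: a 10-point AOFAS difference, SD 12, alpha 0.05 and power 0.8 give 23 patients. After 20% dropout the total is 56, raised to 60 for the blocks of ten. The same section cites 8.36 points as the clinically significant difference in AOFAS.

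**The concern.** *Similar* and *better* are different claims with different null hypotheses and decision rules. One primary analysis cannot serve both, and a later analysis plan that inherits its hypothesis from this text has to pick one without guidance.

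The Mann-Whitney test at p < 0.05 addresses *better*. Nothing in the plan addresses *similar*: failing to reject a null of no difference does not show that the difference is small. Because *similar* is in print as the main hypothesis, a non-significant result could be presented as confirming it.

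This matters most in stratum I, where the question is whether a cast can replace surgery. The Discussion presents the trial as the first randomized comparison of the two. A cast that is worse by a clinically significant amount could be reported as equally good because the sample was too small to show the deficit.

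**Working it through.** **Inputs.** From the Power analysis: difference 10, SD 12, alpha 0.05, power 0.8, dropout 20%, 60 recruited, cited clinically significant difference 8.36. Assumed: 1:1 allocation, which is not stated. The margin is also an assumption, since none is given; 8.36 and 10 are the only candidate figures in the article.

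**1. The plan's own figure.** Two-sided test of difference, normal approximation:

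n per arm = 2 × [12 × (1.960 + 0.842) / 10]² = 22.6, so 23. This matches. A one-sided test would give 18.

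Dropout: 23 × 1.2 = 27.6, so 28 per arm and 56 for one two-arm comparison. This matches the stated 56, but the text applies that total to both strata. Both readings are therefore carried:
- 60 per stratum: 30 per arm × 0.8 = 24 evaluable per arm.
- 60 over both strata: 15 per arm × 0.8 = 12 evaluable per arm.

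**2. Chance of a non-significant result when one arm is truly worse.** SE = 12 × √(2/n). The probability is one minus the power of the two-sided t test, from the noncentral t distribution with 2n − 2 degrees of freedom and noncentrality (true difference)/SE. The CI half-width is t(0.975; 2n − 2) × SE.

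| Evaluable per arm | SE | 95% CI half-width | P(p > 0.05), true difference 8.36 | P(p > 0.05), true difference 10 |
|---|---|---|---|---|
| 24 | 3.46 | 2.013 × 3.464 = 6.97 | 34% | 19% |
| 12 | 4.90 | 2.074 × 4.899 = 10.16 | 63% | 50% |

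**3. What the interval could exclude.** At 24 per arm an observed difference of zero excludes a deficit of 8.36 (half-width 6.97), but an observed deficit above 8.36 − 6.97 = 1.39 points does not. At 12 per arm even an observed difference of zero does not exclude 8.36, because the half-width is 10.16.

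**4. Power if *similar* is the aim.** Non-inferiority, arms truly equal, one-sided 0.025:
- Margin 8.36: about 66% at 24 per arm and 37% at 12.
- Margin 10: about 81% and 50%.

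These are the complements of the percentages in step 2 (the noncentrality is the same), so they are the same calculation read the other way and not further evidence.

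For 80% power at margin 8.36: n = 2 × [12 × 2.802 / 8.36]² = 32.3, so 33 evaluable per arm. With dropout, 33 / 0.8 = 41.25, so 42 per arm and 84 per stratum.

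The figures use the t test or normal approximation; under the Mann-Whitney test they would differ slightly.

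**The case against.** The section that states the hypotheses formally and the section that states the test agree on a difference, and the power calculation is compatible with that. The Abstract is the outlier, so one could call this a loose summary. That supports the cheap remedy, but it does not remove the conflict: both texts are current, and the Abstract labels its version the main hypothesis.

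Four stronger readings are tempting, and the document does not support them.

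- *A reader might infer that the sample size fits a superiority trial only.* It does not. Non-inferiority with a 10-point margin, SD 12, one-sided 0.025, 80% power and truly equal arms uses the same formula and also needs 23 per arm. What points to a test of difference is the analysis without a margin. A 10-point margin would, however, exceed the article's own 8.36.
- *A reader might infer that some version of the hypothesis fits whatever the data show.* A significant result favouring ORIF fits neither version, because the Hypotheses section is directional.
- *A reader might infer that the sponsor plans to read p > 0.05 as similarity.* The article does not say so. It is a risk. The promised 95% confidence intervals reduce it, but only partly while there is no reference value to read them against.
- *A reader might take the 12-per-arm figures as settled.* They hold only if the 60 patients cover both strata, which the wording leaves open. At 24 per arm the position is clearly better.

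**Conclusion.** The contradiction stands for both strata, and the *similar* version has no analysis behind it that could establish it. The fault lies in the unresolved hypothesis and the absent rule for similarity; the sample-size arithmetic reproduces.

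The size of the risk, with SD 12, 1:1 allocation and 20% dropout: a true deficit equal to the cited clinically significant difference would go undetected in about a third of trials at 24 evaluable per arm, and in nearly two thirds at 12. Which of these applies depends on an ambiguity in the Power analysis that the article does not resolve.

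**What to change.** Before any comparative data are seen, state one hypothesis per stratum and use it in both the Abstract and the Hypotheses section. There are two routes.

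**Keep superiority (cheap).** Retain the Hypotheses section, replace *similar* in the Abstract, and add two sentences: p > 0.05 is inconclusive, and similarity will be claimed only if the 95% CI for the AOFAS difference excludes 8.36 points. Say whether that means excluding a deficit for the cast (stratum I) or PA (stratum II), or a difference in either direction. The cost is wording only; no patients or procedures are added.

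**Adopt *similar* as the aim.** Pre-specify and justify a non-inferiority margin no larger than 8.36 points, base the conclusion on the confidence interval, and replace the stated 80% power with about 66% at 24 per arm or about 37% at 12 per arm, for truly equal arms. This is more than wording. Keeping 80% power takes about 33 evaluable per arm (84 recruited per stratum). Recruitment began in 2011 and 51 patients had been included by October 2017, so it would be a late change of design. If the sponsor does not enlarge the trial, it should state openly that it accepts the lower power.

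Either way, the Power analysis should say whether the 60 patients are per stratum or in total.
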